### Safety evaluation indexes

The safety evaluation indexes included postoperative intrauterine infection (fever, abnormal vaginal discharge), the duration of vaginal bleeding, lower abdominal pain (Visual Analogue Scale/Score, VAS pain score), and allergic reactions. VAS is a commonly used scoring standard for evaluating pain intensity in the clinic. This method is classified according to the impact of pain on patients’ sleep. If pain symptoms do not affect patients’ sleep, patients belong to mild pain. If the pain symptoms will affect the patient’s sleep, but the patient can still fall asleep, the patient belongs to moderate pain. If the pain symptoms make the patient unable to sleep, the patient belongs to severe pain symptoms. Patients will be asked about the degree of pain 2–3 days after hysteroscopy.

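### The pain safety index is called a VAS score but is defined only as three grades of sleep disturbance, so the label is wrong and the comparison is coarser than it needs to be

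*Protocol article*

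**What the plan says.** Everything on this index stands in one paragraph of the protocol article, Safety evaluation indexes.

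- The index is named as "lower abdominal pain (Visual Analogue Scale/Score, VAS pain score"). It is one of four, beside intrauterine infection, duration of vaginal bleeding and allergic reactions.
- The instrument is introduced as a measure of intensity: "VAS is a commonly used scoring standard for evaluating pain intensity in the clinic".
- The operational definition follows: "This method is classified according to the impact of pain on" sleep. If pain does not affect "sleep, patients belong to mild pain". If sleep is affected "but the patient can still fall asleep, the patient belongs to moderate pain". The top grade reads: "If the pain symptoms make the patient unable to sleep, the patient belongs to severe pain symptoms".
- Timing: "Patients will be asked about the degree of pain 2–3 days after hysteroscopy".

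No line length, numeric range, end anchors or cut-points are given, and no other section describes a numeric pain score. The section on statistical analysis methods assigns a t-test to normally distributed measurements and a rank-sum test to ordinal categories. All tests are two-sided at 0.05.

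**The concern.** The instrument named and the instrument defined differ. A visual analogue score records how intense the pain is. The grades record how far pain interferes with sleep. The two need not agree, because pain felt mainly by day can be considerable and still leave sleep intact.

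The lowest grade also holds two different groups: women with no pain, who have no level of their own, and women with any pain that lets them sleep. A shift from no pain to noticeable pain that spares sleep cannot be seen.

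Two things are at stake. First, a result published as a VAS score would carry the wrong label and could not be set beside real VAS data. Second, pain is one of only four named safety indexes for a material that the abstract describes as new to obstetrics and gynecology, so the comparison should be able to show extra pain if it exists. The label also bears on the analysis: under the plan's own rules, a measured score and an ordinal grade go to different tests.

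**Working it through.** **Plan's own figure.** None exists. The documents give no effect, SD, grade frequencies or power for pain. What follows is illustration under stated assumptions.

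**Inputs from the documents.** 83 evaluable and 100 enrolled per arm (Sample size); two-sided 0.05 and the rank-sum test for ordinal data (Statistical analysis methods).

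**Assumed inputs.** Pain on a 0–10 scale, normal with SD 2, clipped at 0 and 10; control mean m from 2 to 3; experimental mean m + 1. For the graded version, two cut-points turn the same score into mild, moderate and severe. This lets sleep grades follow pain intensity perfectly.

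**Why grading loses information.** The share in the lowest grade is Φ((cut − mean)/2).

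- Lower cut 4, m = 2: control Φ(1.0) = 84%, experimental Φ(0.5) = 69%.
- Lower cut 4, m = 3: control Φ(0.5) = 69%, experimental Φ(0) = 50%.
- Lower cut 2, m = 2: control Φ(0) = 50%, experimental Φ(−0.5) = 31%.

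With a high lower cut, most women in both arms share one value, and differences among them are lost.

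**Simulated rank-sum power, 83 per arm, 1-point shift, m from 2 to 3.**

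| Analysed as | Power |
|---|---|
| Score itself | about 87–88% |
| Three grades, cuts 4 and 7 | about 63–75% |
| Three grades, cuts 3 and 6 | about 75–80% |
| Three grades, cuts 2 and 5 | about 79–84% |

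Repeated runs differ by a few points. For cuts 2 and 5, most values lay at 79–82%, and 84% was the highest seen. For a 0.75-point shift, power is about 64–66% on the score, 39–51% with cuts 4 and 7, and 56–59% with cuts 2 and 5.

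**Second check, without a 0–10 scale.** Take a normal latent intensity and the shift that gives a t-test 80% power: d = (1.960 + 0.842) × √(2/n). This is 0.435 SD at n = 83 and 0.396 SD at n = 100. The rank-sum test on the continuous score then has about 77–79% power. On three grades:

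| Assumed control shares, mild/moderate/severe (%) | n = 83 | n = 100 |
|---|---|---|
| 33/33/33 | 69% | 68% |
| 60/30/10 | 67% | 68% |
| 70/20/10 | 64% | 64% |
| 80/15/5 | 57% | 57% |
| 90/8/2 | 44% | 43% |

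Both checks agree on direction. The size depends on how many women fall in the lowest grade, which the documents do not tell us.

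**The case against.** **A number may be recorded after all.** The sleep wording could be a set of verbal labels attached to a VAS value, and the case report form belongs to the full protocol, which is not shown. This is possible, and it limits what can be said about practice. It does not remove the point. The article does not leave the method unstated; it spends several sentences defining one, and what it defines is not a VAS. If a number is collected, the paragraph still needs correcting.

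**Pain is still captured.** A reader might infer that pain is not measured at all. The documents do not support that: pain is graded at a planned contact, and the Adverse events section says that all adverse events are evaluated and recorded in detail, which gives notable daytime pain a second route. What is missing from the text is the VAS value.

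**The power loss is set by the chosen cut-points.** This stands. Taking cuts of 4 and 7 alone, one might call a loss of some 12 to 25 percentage points a minimum, because the grades are assumed to follow pain perfectly. It is not a minimum: with cuts of 2 and 5 and equally perfect tracking, most runs lose only about 6 to 9 points.

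**Pain carries no formal hypothesis.** This is also true. The trial is sized on the repair rate alone, and no section plans a claim of no difference in pain. The planned rank-sum test suits ordered grades, so the fault lies in the definition and label of the measurement, not in the test.

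**Conclusion.** The point holds as a contradiction between label and definition. The article names a VAS score of pain intensity and defines a three-level sleep-interference grade with no level for no pain. A result reported as VAS would be mislabelled, and the grading is less able to show extra pain with the scaffold.

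Only the direction of that loss is firm. Under the stated assumptions (83 per arm, SD 2, control mean 2–3, 1-point shift), rank-sum power falls from about 87–88% to somewhere in 63–84%. The range reflects the choice of cut-points and is neither a floor nor an estimate for this trial.

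This is a minor point with a cheap correction. Primary and secondary outcomes are unaffected.

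**What to change.** At the contact already planned 2–3 days after hysteroscopy, record an actual VAS value with its range stated (0–10 or 0–100 mm). Compare the arms on that score, using the rank-sum test if it is not normally distributed. Say so explicitly for this index, because the statistical section names a chi-square test for non-normal measurements. Keep sleep disturbance as a separate ordinal item under its own name.

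If only grades are collected, rename the index as a sleep-interference grade, add a no-pain level, and analyse it with the rank-sum test the plan already assigns to ordinal variables. Drop the VAS label from the protocol and from any report.

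The cost is one extra number per patient at an existing contact and a wording correction. The fallback needs one added answer level and the renaming.

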### Sample size

The sample size calculation is based on the repair rate of moderate/severe IUA. Based on the fact that the repair rate of Foley balloon placement was 47–71.67% [8, 19], we assume that the effective rate of uterine adhesion repair can reach 80%. According to the calculation method for several cases related to the superiority study, the number of samples was estimated as 83, with *α* = 0.025 (one-sided) and *β* = 0.2. A sample size of 83 prospectively enrolled participants in each randomization arm. In consideration of a dropout rate of 20%, we will enroll 100 participants in each group response.

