Endometrial injury can easily cause IUA, which primarily manifests as an endometrial basal layer injury caused by trauma, infection, and other factors, resulting in the dysfunction of functional endometrial repair; in turn, this will lead to the proliferation of fibrous connective tissue and endometrial fibrosis as well as partial or total intrauterine occlusion [2, 4]. According to the consensus of Chinese experts on the clinical diagnosis and treatment of intrauterine adhesions [5], at present, for patients suffering from infertility, recurrent abortion, and oligomenorrhea and for those with special fertility requirements, transcervical resection of adhesion (TCRA) can be conducted as a preferred treatment (recommendation level: C). Moreover, TCRA combined with an intrauterine device (IUD), Foley balloon support, or estrogen and progesterone replacement therapy has shown degrees of anti-adhesion value, although their effects are variable. An IUD placement after moderate and severe IUA could reduce the formation rate of re-adhesion to 35% [6] (evidence level: I). But meta-analysis showed that the menstrual improvement rate ranged between 28.5 and 100%. Several studies have indicated significant differences in this regard [7]. In addition, although an intrauterine balloon can make the total effective rate of IUA repair reach 71.67% [8] and improve the menstrual rate up to 81.4–95% [9, 10], the shape of the balloon used in clinics is not suitable for the intrauterine cavity, which makes it difficult to block the wound completely. Moreover, if the intrauterine balloon is not placed properly, intimal ischemia and necrosis may occur, which will impact intimal regeneration and repair. In particular, for patients with severe IUA, due to endometrial basal layer damage, reduced residual normal endometrial tissue, and poor regeneration ability, the recurrence rate of postoperative adhesion can still be as high as 62.5%, while the success rate of pregnancy will range between only 22.5 and 33.3% [11]. Therefore, establishing an anti-adhesion method that can promote the repair of endometrial injury is of great significance.

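### Enrolling 100 per arm leaves 80, not the required 83, after 20% dropout, and 83 per arm gives 80% power only if the unstated control rate is about 60% or lower

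*Protocol article*

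**What the plan says.** The Sample size section of the protocol article sets out the calculation in a few sentences.

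- Control rate: "Based on the fact that the repair rate of Foley balloon placement was 47–71.67" per cent, from two cited sources.
- Target: "we assume that the effective rate of uterine adhesion repair can reach 80" per cent. I read this as the rate expected in the scaffold arm.
- Error rates: "with *α* = 0.025 (one-sided) and *β* = 0.2".
- Result: "A sample size of 83 prospectively enrolled participants in each randomization arm".
- Allowance for losses: "In consideration of a dropout rate of 20%, we will enroll 100 participants in each group response".

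The section names no single control rate, no superiority margin and no formula. The Background returns to the upper figure, saying that "an intrauterine balloon can make the total effective rate of IUA repair reach 71.67" per cent. The balloon alone is the control treatment in this trial.

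**The concern.** There are two separate problems in the one paragraph.

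First, the enrolment target does not deliver the paragraph's own evaluable number at its own dropout rate. This is a slip in the headline recruitment figure.

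Second, a sample size for comparing two proportions needs one control rate, and the text supplies a range almost 25 points wide (71.67 − 47 = 24.67). The assumed difference from 80% is 33 points at one end and 8.33 at the other, so the required number changes more than tenfold across the range. A reader cannot tell which rate gave 83, nor over how much of the range the stated beta of 0.2 is met. If the balloon performs towards the top of the cited range, a non-significant result would say little about the scaffold, and the paragraph as written does not warn of this.

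**Working it through.** **Inputs from the Sample size section:** one-sided alpha 0.025 (z = 1.960); beta 0.2 (z = 0.842); experimental rate 0.80; control rate 0.47 to 0.7167; 83 evaluable and 100 enrolled per arm; dropout 20%. Allocation is 1:1 (Randomization and allocation). **My assumptions:** pooled-variance two-proportion test and no superiority margin, since none is stated.

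**Step 1: the dropout allowance.**

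- The plan's figure is reproduced by 83 × 1.2 = 99.6, rounded to 100.
- The allowance that leaves 83 is 83/(1 − 0.20) = 103.75, rounded up to 104 (208 in total instead of 200).
- With 100 enrolled and 20% lost, 100 × 0.8 = 80 remain, 3 short of 83.
- The dropout that 100 can absorb is 1 − 83/100 = 17%.

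**Step 2: reproducing 83.** With p̄ the mean of the two rates,

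n = [1.960·√(2p̄(1 − p̄)) + 0.842·√(p_c(1 − p_c) + p_e(1 − p_e))]² / (p_e − p_c)²

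At p_c = 0.60 and p_e = 0.80, p̄ = 0.70. The numerator is (1.960·√0.42 + 0.842·√0.40)² = (1.270 + 0.532)² ≈ 3.249. Dividing by 0.04 gives 81.2, so 82 per arm, close to the stated 83. Solving for exactly 83 gives a control rate of 0.602 (unpooled variance 0.606, arcsine 0.604, continuity-corrected 0.589).

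This does not identify what the sponsor assumed. A continuity-corrected test at 59% gives 84, and a 50% control rate with a 10-point margin (unpooled) gives 81.

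**Step 3: required number and power across the cited range.** Power is Φ{[(p_e − p_c)√n − 1.960·√(2p̄(1 − p̄))] / √(p_c(1 − p_c) + p_e(1 − p_e))}.

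| Control rate | n per arm for 80% power | Power, 83 per arm | Power, 80 per arm |
|---|---|---|---|
| 47% (bottom of range) | 33 | 99.6% | 99.4% |
| 55% | 54 | 93.8% | 92.9% |
| 59.3% (midpoint) | 77 | 83.2% | 81.8% |
| 60% | 82 | 80.9% | 79.4% |
| 65% | 138 | 58.2% | 56.6% |
| 70% | 294 | 31.7% | 30.8% |
| 71.67% (top of range) | 414 | 23.9% | 23.2% |

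The required number differs by a factor of 414/33 ≈ 12.5 between the two ends.

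**Step 4: the two problems compared.** At 60% versus 80%, the dropout slip costs 80.9 − 79.4 = 1.5 points of power. Moving the control rate from 60% to 65% costs 80.9 − 58.2 = 22.7 points. Analysing all 100 per arm would not change the picture at the top of the range: power at 71.67% would be 27.9%.

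**The case against.** The dropout slip matters little in practice. With 80 evaluable per arm, power at the midpoint of the range is still 81.8%, and no conclusion of the trial turns on three women per arm. That is right, and it limits the weight of this part. The arithmetic is still wrong as printed.

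A reader might infer that the stated power holds only at a control rate of exactly 60%. The figures do not support that: power is 80% or more at every control rate from 47% to about 60%, roughly the lower half of the range.

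A reader might also infer that the trial has 24% power. That is not supported either. The figure belongs to the top of a two-source range, and the Background's wording for 71.67% is that of a level that can be reached. The documents do not show that the source's total effective rate uses this trial's definition of effective repair (a fall of at least 4 AFS points) or a comparable population. The Background also reports recurrence as high as 62.5% in severe adhesions, which gives no reason to expect the top of the range. Planning near the middle of a range is ordinary, and on these assumptions 83 slightly exceeds the 77 needed at the midpoint.

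Finally, this is a condensed article, and a fuller protocol may name the planning rate. That softens the second part but does not remove it. The article gives alpha, sidedness, beta, the target rate, the resulting number and the dropout, yet prints a range for the input on which the result depends most.

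**Conclusion.** The point holds as a moderate correction. It is not grounds for calling the trial underpowered.

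- The enrolment figure is wrong at the plan's own inputs: 100 enrolled leaves 80, and keeping 83 needs 104. This needs no assumption beyond the stated 83 and 20%.
- The 80% power claim is unqualified where it needs to be qualified. It holds up to a control rate of about 60% and fails above that, over a little under half of the cited range ((71.67 − 60)/24.67 ≈ 47%). This rests on the pooled test, no margin, and 80% being the scaffold-arm rate. Unpooled, arcsine and continuity-corrected versions move the threshold only between about 59% and 61%; a non-zero margin would lower it.
- It would go too far to say that the sponsor assumed 60%. That value is inferred, and other unstated settings give nearly the same number.

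**What to change.** 1. Restate the enrolment sentence in one of three ways: 100 per arm, covering 17% dropout; 100 per arm, leaving 80 evaluable after 20% dropout, with the power this gives (79.4% if the control rate is 60%); or 104 per arm, if the sponsor prefers to keep both 83 and 20%.
2. State the single control rate, the superiority margin (including zero, if that was used) and the formula that actually produced 83. The 60% should not be written in unless it was the planning value.
3. Qualify the power claim as holding up to that control rate, and show power at the upper end of the cited range as a sensitivity figure. On the assumptions used here, these are 58% at 65%, 32% at 70% and 24% at 71.67%.

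The cost is a few sentences in one paragraph. Only the 104 option adds recruitment: 4 women per arm, 8 in total. The endpoint, the test and the treatment of patients are unaffected.

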### Adverse events

Adverse events (AEs) referred to any adverse medical events experienced by a participant during the study; it concerned their participation in the research, regardless of its relationship with research intervention. Serious AEs (SAEs) referred to events related to a participant that occurred during the study and met any of the following criteria: death, a life-threatening event, a severe or persistent disability, requiring or prolonging hospitalization, disability, congenital malformation, or any other events considered serious by the principal investigator. All AEs were evaluated and recorded in detail. All SAEs were reported to the principal investigator within 5 days, and appropriate measures were taken immediately. Any SAEs that were not intentional and that were possibly related to study interventions were reported within 24 h. In such cases, the ethics committee determined whether an AE or SAE was related to the study intervention and whether it was necessary to breach the blinding guidelines.

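### Any SAE may take up to 5 days to reach the principal investigator, and the 24-hour clock covers only events already sorted as possibly related

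*Protocol article*

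**What the plan says.** The protocol article deals with reporting in one paragraph, under Adverse events.

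- General rule: "All SAEs were reported to the principal investigator within 5 days, and appropriate measures were taken immediately".
- Faster rule for a subset: "Any SAEs that were not intentional and that were possibly related to study interventions were reported within 24 h".
- Causality: "In such cases, the ethics committee determined whether an AE or SAE was related to the study intervention". The same sentence gives the committee the decision on breaking the blind.
- Handling of all adverse events: "All AEs were evaluated and recorded in detail". No assessor is named and causality is not mentioned.
- Seriousness: the usual criteria, including death and life-threatening events, plus a catch-all for "any other events considered serious by the principal investigator".

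**The concern.** The 24-hour limit depends on someone first judging the SAE possibly related. Under the rule as written, that judgement comes before the principal investigator need have heard of the event. The paragraph gives the first judgement to nobody by name; the one body it names for relatedness is the ethics committee. An SAE that front-line staff first take to be unrelated stays on the 5-day route, and nothing in the rule brings the principal investigator in sooner to correct that view. The promise of immediate measures sits in the 5-day sentence, so it is unclear what immediacy is measured from.

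This matters here for two reasons. The Abstract describes the study as the first use of ECM scaffolds in obstetrics and gynecology, so experience in this setting for calling an event unrelated is limited. Also, both arms have hysteroscopic adhesiolysis and a balloon, so a serious infection in the scaffold arm could be put down to the operation. Other women could receive the scaffold before the principal investigator knew of such an event.

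**Working it through.** **Inputs, all from Adverse events**

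- Limit for any SAE to reach the principal investigator: 5 days.
- Limit for unintended, possibly related SAEs: 24 h.
- Start of either clock: not stated.
- Recipient of the 24-hour report: not stated.

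There is no figure of the plan's own to reproduce.

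**Arithmetic**

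- General limit in hours: 5 × 24 = 120 h.
- Ratio of the limits: 120 / 24 = 5.
- Largest gap between them: 120 − 24 = 96 h.

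**What the rule allows for an SAE that is in fact possibly related**

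Both clocks are assumed to start at the same moment, except in the last row.

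| Who sorts the event, and how | Latest time allowed by the rule | Beyond the 24-hour limit |
|---|---|---|
| Site staff judge it possibly related at once | 24 h | 0 h |
| Site staff first judge it unrelated | 120 h | up to 96 h |
| Nobody sorts it until the principal investigator hears | 120 h | up to 96 h |
| As the row above, with the 24-hour clock starting when the principal investigator hears | 120 h to the principal investigator, then 24 h | 0 h formally |

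In the last row the fast report can come 120 + 24 = 144 h after the event and still comply.

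**Which filter does the work**

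The fast rule has two conditions. Read literally, almost any SAE is unintended, so the first condition removes little. The second, possible relatedness, decides the route. It is also the condition most open to a mistaken first view.

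**The principal investigator's role in the same paragraph**

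The catch-all criterion makes an event serious because the principal investigator considers it so. For those events the principal investigator must already know. For events that are serious by the listed criteria, the same person may be told up to 120 h later. The paragraph thus relies on the principal investigator's judgement for seriousness but does not provide for it at the point where relatedness sets the reporting route.

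**The case against.** The strongest reply is that this is an ordinary tiered scheme: a general 5-day limit with a stricter limit for a subset. That reading is fair, and on it the two sentences are compatible.

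A reader might infer more than the text supports in three places.

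- **That the two clocks contradict each other or cannot both be applied.** They can. If site staff make the first judgement correctly, the overrun is 0 h.
- **That the ethics committee must decide relatedness before anyone has told it of the event.** The text does not say this. The sentence on the committee follows the 24-hour sentence and refers back to it, so the natural reading is that the committee rules on events already reported fast. It may even be the recipient. Possible relatedness is also a lower threshold than the committee's determination, so the fast clock need not wait for the committee.
- **That a scaffold infection or allergic reaction would usually take the slow route.** Both are listed under Safety evaluation indexes, so staff are told to look for them, and many such events would be recognised as possibly related.

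Some further points also stand. Recruitment is from one hospital centre, which makes long unawareness less likely in practice. The Abstract notes wide use of the scaffold in general surgery and neurosurgery, and novelty may make staff more cautious, not less. The withdrawal criteria give safety discontinuation to the sponsor and mention discontinuation by the ethics committee, so stopping is not said to depend on the principal investigator. Recipients, clock starts and the name of the first assessor may be in the full protocol or the standard operating procedures mentioned under Data management; their absence from an article is not the point here.

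The objection does not remove the stated rule itself. The article gives every SAE up to 5 days to reach the principal investigator and lets an event off that limit only after a favourable first sorting. A fuller document could explain those sentences, but they would still read as they do.

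**Conclusion.** The point holds as a weakness in a stated safety-reporting rule. An SAE first judged unrelated can take up to 120 h to reach the principal investigator. If that first judgement was wrong, the delay is up to 96 h beyond the limit meant for such events; if site staff sort it correctly, it is 0 h beyond. The range rests on two assumptions: that both clocks start together, and that the condition on intention means unintended, not unexpected. The article does not say how often a first judgement would be wrong, so no expected delay can be given.

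The change is worth making because it protects participants at little cost. It has no bearing on the sample size of 100 per group or on the analysis of the primary outcome.

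**What to change.** Reconcile the reporting sentences under Adverse events into one rule:

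1. Every SAE reaches the principal investigator within 24 h of any site staff becoming aware of it, whatever the first view of relatedness. This replaces the 5-day limit and fixes the start of the clock.
2. The principal investigator makes and records the initial relatedness judgement.
3. Possibly related SAEs go to the ethics committee, which reviews relatedness and keeps its present decision on breaking the blind.

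If the full protocol or the operating procedures already say this, the article's text should be brought into line with them.

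The cost is a sentence or two of protocol text and a short addition to site training. The small downside is that some unrelated SAEs will be reported sooner than they need to be.
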